## Abstract

**Background:**

Physicians work in a highly demanding work setting where ongoing changes affect their work and challenge their employability (ie, their ability and willingness to continue working). In this high-pressure environment, physicians could benefit from proactively managing or *crafting* their careers; however, they tend not to show this behavior. The new concept of career crafting concerns proactively making choices and adapting behavior regarding both short-term job design (ie, job crafting) as well as longer-term career development (ie, career self-management). However, so far, no intervention studies have aimed at enhancing career crafting behavior among physicians. Given that proactive work and career behavior have been shown to be related to favorable outcomes, we designed an intervention to support career crafting behavior and employability of physicians.

**Objective:**

The objectives of this study were to describe (1) the development and (2) the design of the evaluation of a randomized controlled career crafting intervention to increase job crafting, career self-management, and employability.

**Methods:**

A randomized controlled intervention study was designed for 141 physicians in two Dutch hospitals. The study was designed and will be evaluated based on parts of the intervention mapping protocol. First, needs of physicians were assessed through 40 interviews held with physicians and managers. This pointed to a need to support physicians in becoming more proactive regarding their careers as well as in building awareness of proactive behaviors in order to craft their current work situation. Based on this, a training program was developed in line with their needs. A number of theoretical methods and practical applications were selected as the building blocks of the training. Next, participants were randomly assigned to either the waitlist-control group (ie, received no training) or the intervention group. The intervention group participated in a 4-hour training session and worked on four self-set goals. Then, a coaching conversation took place over the phone. Digital questionnaires distributed before and 8 weeks after the intervention assessed changes in job crafting, career self-management, employability, and changes in the following additional variables: job satisfaction, career satisfaction, work-home interference, work ability, and performance. In addition, a process evaluation was conducted to examine factors that may have promoted or hindered the effectiveness of the intervention.

**Results:**

Data collection was completed in March 2020. Evaluation of outcomes and the research process started in April 2020. Study results were submitted for publication in September 2020.

**Conclusions:**

This study protocol gives insight into the systematic development and design of a career crafting training intervention that is aimed to enhance job crafting, career self-management, and employability. This study will provide valuable information to physicians, managers, policy makers, and other researchers that aim to enhance career crafting.

**International Registered Report Identifier (IRRID):**

RR1-10.2196/18432

## Introduction

Physicians work in a highly demanding work setting where ongoing changes affect their work. Physicians’ work environment is characterized by high work pressure and other stressors [1]. This challenges physicians’ ability and willingness to continue to work until the retirement age in their current profession [2] (ie, their employability [3]). Recent studies show that the employability profile of physicians and other workers in the health care sector is relatively low compared to employees in other sectors. Specifically, in a study among 42,613 health care workers in the Netherlands, 47% of them thought it was possible to find employment beyond their current employer, compared to 57% of employees in other sectors; 52% of health care workers regularly perceive a high physical workload, compared to 38% of employees in other sectors; and 19% of health care workers often perceive a high emotional workload, compared to 7% of employees in other sectors [4].

In order for employees to successfully navigate within this complex environment, they must proactively take control over their working life by creating a resourceful, healthy, and motivating environment for themselves [5]. This can be done through career crafting, which is a relatively new concept in the literature, and is defined as “individuals’ proactive behaviors aimed at optimizing career outcomes through improving person-career fit” [6]. Career crafting entails both choices and changes to the current work environment (ie, job crafting) as well as actions focused on longer-term career design (ie, career self-management) [6]. Job crafting refers to the self-initiated behaviors that employees take to shape, mold, and change their jobs [7-9]. For example, people can craft social resources such as support or they can optimize tasks or situations that are hindering. An example of job crafting is limiting tasks that drain energy, such as reducing the time spent on meetings by 15 minutes per meeting. Career self-management is defined as the extent to which employees proactively develop their careers as expressed by diverse career behaviors [10]. An example of career self-management is networking behavior, in which someone proactively approaches others who can be helpful in shaping their career. Career crafting entails the combination of both types of behaviors. For example, an employee may reduce energy-draining activities (ie, through job crafting) by communicating firmer boundaries in meetings (eg, “I have 30 minutes for this meeting; what are our highest priorities?”). The time thus gained is used to proactively network with someone from another organization (ie, career self-management), who is employed in a position that is of interest to the employee, to learn about how he or she managed to get that position.

Career crafting is considered an important individual behavior aimed at safeguarding the sustainability of one’s career over time [6]. This suggests that career crafting may possibly enhance employability. However, empirical evidence about the antecedents and consequences of career crafting is lacking and requires further examination. Previous studies have found that career crafting behaviors such as job crafting and career self-management fulfil important roles in contemporary careers and result in beneficial outcomes [11,12]. Previous studies found that career crafting behaviors are beneficial to the individual, as reflected in enhanced work engagement [13], well-being [14], meaningfulness, and job satisfaction [15], as well as to the organization, as reflected in enhanced performance [16]. This makes it worthwhile to invest in an intervention program that enhances physicians’ career crafting and employability, which is urgent in today’s health care career context.

Three gaps exist in the current literature. First, despite the increasing importance of proactive career behaviors, to our knowledge, as yet no intervention studies have aimed at enhancing career crafting. Career adaptability training for graduates [17] focused on facilitating the school-to-work transition but did not examine how to stay employable within a work context. That study and other existing career interventions had a different focus (eg, career coaching or counseling) than the subject of our study or showed methodological weaknesses [18]. These studies, for instance, used a cross-sectional study design [19], lacked a control group [20-22], or did not assign participants randomly to a control or treatment group, as shown in a meta-analysis by Whiston et al [23].

Second, career studies have mainly focused on employees in general [24], while employees in different jobs have been shown to have different career trajectories and employment opportunities [25]. Paying attention to physicians’ careers is important for two reasons. First, some studies describe their career choices as serendipitous or circumstantial [26] and mention that physicians are neither actively engaged in career planning nor being stimulated to do so [27,28]. Other studies have shown that attention on careers is beneficial for employee job satisfaction [22] and may help employees to keep up with a fast-changing work environment [29]. Second, physicians’ career trajectories are different from those of other employees. Physicians usually finish their medical training around the age of 30 years and work as medical specialists for the next 30-35 years of their career. Although their high level of education may stimulate career possibilities, the specialized nature of their work tends to reduce their employment opportunities and may, thus, result in physicians often having the same job until retirement [25]. Relevant career opportunities for physicians should, therefore, not only focus on promotion, since possibilities for this are limited, or on external opportunities (eg, changing jobs or organizations), but they should also include possibilities of internal career opportunities (eg, changing work content or tasks). Focusing on physicians’ career content may help physicians in developing coping skills to effectively deal with the challenges presented by their work environment. This seems important as research has shown that some physicians are insecure about their competencies to fulfil nonclinical tasks, such as teaching, managerial skills, and financial skills, for which they are not primarily educated [30,31]. The career crafting training developed in this study is likely to fit physicians’ needs, since their needs have been identified and because the content of the training has been developed in collaboration with physicians.

Third, most intervention studies mainly focus on the analysis of outcomes and lack a systematic process evaluation [32,33]. This may be partly explained by the absence of an evidence-based framework that describes the elements that need to be included in process evaluations. Nevertheless, process evaluation is important as it helps us to understand why parts of an intervention result in a certain outcome and shows how research findings can be used to guide practice [32].

In responding to these knowledge gaps, this study makes the following contributions. This study contributes to the literature on proactive career behavior by elaborating on the development and design of the evaluation of a career crafting training intervention. In doing so, the specific needs and challenges that physicians face are taken into account, which increases the practical utility of this intervention. This paper elaborates on the systematic process in which this career intervention is developed for, and in collaboration with, physicians. Furthermore, the research protocol discusses a framework to conduct a process evaluation, based on the current literature. The objectives of this study are to describe (1) the development and (2) the design of the evaluation of a randomized controlled career crafting intervention developed for physicians to increase job crafting, career self-management, and employability.

## Methods

### Overview

The intervention was developed in a systematic way, using elements of the intervention mapping (IM) protocol. IM is a widely accepted methodology for planning theory-based and evidence-based health promotion programs [34] and has been used in numerous studies, eg [35], [36]. IM consists of six steps: (1) needs assessment, (2) definition of program objectives, (3) methods and practical applications, (4) intervention program development and pilot test, (5) adoption and implementation, and (6) evaluation. The completion of every step creates a product that is the guide for the subsequent step [34]. Although these steps suggest that this is a linear process, moving back and forth between the steps is part of the process.

### Step 1: Needs Assessment

The first step of IM was to assess and understand the problem and needs of the participants [34]. This intervention was custom-made in close collaboration with potential participants, physicians, and other stakeholders, such as managers of physicians who also work as physicians. There is widespread agreement that a participative approach in the design of interventions is promising. Employees are often familiar with the problems and the best solutions in their work context, and people can identify better with a project if they perceive themselves to be the agents of change rather than the objects of change [37].

In an earlier stage of this study, 40 face-to-face exploratory interviews were conducted to examine physicians’ experiences with job crafting, career self-management behavior, and employability. Out of the 40 interviews, 27 (68%) were done with the target population, namely physicians, and 13 (33%) were conducted with their managers who also worked as physicians. The results of these interviews were discussed and interpreted by a planning group. This group consisted of the researchers of this study, a senior board member and a physician who also worked as a manager in the academic hospital, and two physicians and a senior board member of the general hospital. The reflections of the planning group were also discussed in both hospitals with people from the human resources department who were familiar with current policies and trainings for physicians. The interviews revealed that physicians lack attention for job crafting and career self-management. Moreover, employability was hardly discussed or thought of in this occupational group. Despite this, physicians and their managers emphasized the importance of finding ways to increase physicians’ employability. They described several challenges: dealing with a high workload, rapid technological developments, finding a healthy work-life balance, the need to fulfil nonmedical-related tasks (eg, educational tasks or being part of certain committees), and the repetitive character of their tasks, which challenged their motivation in the longer run. Both physicians and managers mentioned that these challenges affected their ability and/or willingness to continue to work in their profession. Some physicians also indicated that support in these areas would be helpful, since a focus on these themes was not part of their standard medical training. Career crafting training, which helps them to cope with their current work environment and prepare them for their further career, is therefore expected to be in line with their needs.

### Step 2: Definition of Program Objectives

The next step involved specifying the change objectives. This included what must be changed and who must make the change [34]. These were formulated based on the needs that physicians and managers expressed in step 1. The following three program objectives were chosen: the intervention will increase physicians’ (1) job crafting behavior, (2) career self-management behaviors, and (3) employability. Following the IM approach, three personal determinants were identified to realize behavioral change in order to reach these objectives [38]. These were awareness of the importance of investing in job crafting, career self-management, and employability; knowledge about these topics; and learning the skills to know how these investments can be made.

### Step 3: Methods and Practical Applications

In the third step, methods and practical applications were chosen to achieve the objectives [34], based on existing literature and the stakeholder interviews. Multimedia Appendix 1 shows the theoretical methods and the practical applications for each determinant.

### Step 4: Intervention Program Development and Pilot Test

Step 4 included a description of the intervention, completed program materials, and program protocols. The intervention consisted of a 4-hour group training session for diverse groups of physicians with a pre- and postmeasure. This half-day session was a combination of theory, reflection, exercises, and goal setting (see Multimedia Appendix 1). Participants learned the principles of proactive work and career behaviors, and all participants left the session with a plan outlining four small actions for the following 4 weeks.

In order to be successful, the program required pilot testing with intended implementers and recipients [34]. The survey was created and pilot-tested by the first author in 4 face-to-face interviews with physicians and with managers who also worked as physicians. A *think-aloud* method was used, meaning that participants were asked to think out loud when reading the texts and answering the questions. At the end of the interview, some open-ended questions were asked about the survey’s content, wording, and style of addressing physicians. If needed, introduction texts and items were adapted. Then, a list was made including program themes, assignments, and time frame planning. A training program and protocol was drafted, which was pretested in a pilot training session with intended users. A total of 5 physicians participated, who varied as much as possible on variables that might affect the variables of interest (eg, gender and age). The physicians followed the pilot training session and evaluated the training session at the end in a group discussion, based on the following: content, wording, suitability of given examples, and types of exercises. This resulted in optimization of the training content through some adaptations in allocated time and wording to make the content better suited to the perspectives of physicians. Moreover, examples of job crafting and career self-management were added, based on experiences of the physicians.

### Step 5: Implementation

In this step, participants were recruited via presentations in physicians’ staff meetings, word-of-mouth communication in existing networks, and promotions of the training via email. An email with information on the intervention (ie, goal, content, and duration of the intervention) was sent to the heads of departments, who were asked to share the email with physicians on their team. At the same time, the emails were sent to the representatives of physicians, who were asked to send the email to physicians in their department. In addition, accreditation was requested and granted. This means that physicians earned accreditation points (ie, professional development points) when participating in this training, which they need to stay registered. This will likely increase physicians’ extrinsic motivation to participate in this training.

This intervention study started with randomly assigning participants to the waitlist-control group or the intervention group. Two independent randomizations were done using the randomizer function in Microsoft Excel (version 16.41): one for physicians in the academic hospital who were either assigned to the waitlist-control group or intervention group, and one for physicians in the general hospital who were randomized in a waitlist-control group or intervention group. Two independent randomizations enhanced the probability of equally dividing physicians in one hospital to the control or intervention group. This is important given the expectation that physicians from both hospitals differ on characteristics that might affect their career crafting behavior, such as type of contract and the degree of specialization. The advantage of the waitlist-control group is that all physicians received the intervention in the end. They were blind to the condition (ie, waitlist-control group or intervention group) to which they were assigned.

Figure 1 shows the procedure of this experiment. Participants in both the intervention and control groups received an email inviting them to complete the pretest. A total of 1 week after receiving the digital survey, which was sent through the program Qualtrics (version April 2020), physicians in the intervention group received a 4-hour training intervention. In total, 7-14 physicians were planned to attend each training session. After that, they worked on their self-set goals for the next 4 weeks. Then, a coaching conversation took place on the phone. A total of 3 weeks after the coaching conversation, which was 8 weeks after the pretest, physicians in both groups received a link to the posttest.

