#### Participants

The sample size was calculated on the basis of 95% power to reject the null hypothesis with a 2-tailed significance level of 5%. Assigning equal numbers of participants to the intervention and control groups, and based on the effects of job crafting training interventions on job crafting behavior [45,46], a total of 120 physicians (60 in each group) were needed. We aimed for 150 participants, to allow for 20% dropout. We widely communicated the possibility of participating in this intervention study to physicians, as explained in step 5. However, we did not reach all physicians (ie, 685 physicians in the academic hospital and 225 physicians in the general hospital), as we were not invited into all the departments of the hospital to give a presentation about the training content. In the end, 141 physicians participated; 107 physicians (76%) were employed by the academic hospital and 34 physicians (24%) worked in the general hospital.

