#### Data Analysis

Depending on the assumptions for outliers, normality, and sphericity, we are planning to conduct 2-way, repeated-measures multivariate analyses of variance in SPSS (version 25.0 (IBM Corp)), to assess the *time* × *group* interaction effects of the intervention on the main and additional outcome measures. Subsequently, if the tests for assumptions are not violated, we will perform repeated-measures analyses of variance to further examine the effects within the control and intervention groups.

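### Randomisation was done separately in each hospital, but the planned time × group model leaves hospital out: a small loss of efficiency if the hospitals differ in pre-post change

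*Protocol article*

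**What the plan says.** Under Step 5: Implementation, the protocol article describes one randomisation for the academic hospital and another for the general hospital. Its purpose is balance within hospital: "Two independent randomizations enhanced the probability of equally dividing physicians in one hospital to the control or intervention group". The reason is prognostic, namely the expectation that "physicians from both hospitals differ on characteristics that might affect their career crafting behavior", with contract type and degree of specialization as examples. Hospital is the only stratification factor described.

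Under Participants, the strata are given as "107 physicians (76%) were employed by the academic hospital and 34 physicians (24%) worked in the general hospital", 141 in total.

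Under Data Analysis, the plan is "2-way, repeated-measures multivariate analyses of variance in SPSS", used "to assess the *time* × *group* interaction effects of the intervention on the main and additional outcome measures". Repeated-measures ANOVAs within each arm follow. Hospital does not appear in this section as a factor, covariate or stratum.

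**The concern.** A factor judged important enough to shape the randomisation should normally also enter the analysis. When arms are balanced on a factor that predicts the analysed score and the model omits it, variation between the hospitals stays in the error term although it has been removed from the treatment comparison. Standard errors are then too wide and the test is conservative. When balance was only made more likely, a chance imbalance in hospital stays in the estimate.

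This is more than detail left to an unseen analysis plan. The term 2-way fixes the number of factors, and time × group names them. An analysis plan that added hospital would depart from the model stated here.

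At stake are some efficiency and the removal of chance imbalance. The main outcomes concerned are job crafting, career self-management and employability.

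**Working it through.** **Inputs from the protocol article**
- Strata: 107 and 34 of 141 (Participants). 107/141 = 75.9% and 34/141 = 24.1%, matching the stated 76% and 24%.
- Sample size: 60 per group, 95% power, two-sided 5%, 20% dropout (Participants). 120/(1 − 0.20) = 150, as stated.
- One pretest and one posttest, 8 weeks apart (Step 5).

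**Inputs assumed**
- g, the difference between hospitals in mean pre-post change, in within-hospital SDs of change. The article gives no value; the range used is 0 to 1.0.
- d, the treatment effect. No effect size is given, so the 120 cannot be reproduced. Solving backwards from 60 per group gives d = (1.960 + 1.645) × √(2/60) = 0.658 by the normal formula, or 0.664 by the t-test.

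**Step 1. What can enter the test.** With two time points, the time × group interaction for each outcome is the two-group comparison of posttest minus pretest. A hospital effect that is the same at both times subtracts out within each physician. It enters neither the error term nor the estimate. Only g, a hospital × time difference, can matter.

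**Step 2. Scenario A: arms balanced within hospital.** With p = 107/141, p(1 − p) = 0.759 × 0.241 = 0.183.
- Share of change-score variance due to hospital = 0.183g²/(1 + 0.183g²).
  - g = 0.5: 0.0457/1.0457 = 4.4%
  - g = 1.0: 0.183/1.183 = 15.5%
- Actual size of the nominal 5% test = 2 × [1 − Φ(1.96/√(1 − share))].
  - g = 0.5: 1.96/√0.956 = 2.004, giving 4.5%
  - g = 1.0: 1.96/√0.845 = 2.132, giving 3.3%

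A simulation of one outcome (20,000 runs, n = 120, exact 1:1 within hospital, d = 0.664 for power) gives:

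| g | Type I error, without / with hospital | Power, without / with hospital |
|---|---|---|
| 0 | 4.9% / 5.0% | 95.1% / 95.1% |
| 0.25 | 4.8% / 4.9% | 94.7% / 94.9% |
| 0.5 | 4.7% / 5.2% | 94.7% / 95.1% |
| 0.75 | 3.8% / 4.9% | 94.2% / 95.2% |
| 1.0 | 3.3% / 5.1% | 93.3% / 95.2% |

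The simulation standard error near 5% is √(0.05 × 0.95/20,000) = 0.15 points, so 4.7% agrees with the formula's 4.5%. The power loss is about 0.4 points at g = 0.5 and about 2 points at g = 1.0.

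**Step 3. Scenario B: simple coin-flip allocation within each hospital.** Nothing is then restricted, and the unadjusted test keeps its size (simulated at about 5% for g of 0.5 to 1.0). What remains is chance imbalance.
- For Binomial(34, 0.5), P(X ≤ 14 or X ≥ 20) = 39%, the chance of a 14/20 split or worse in the general hospital.
- With 14/20 there and the 107 academic physicians split evenly (53.5 per arm), the general-hospital share is 14/67.5 = 20.7% in one arm and 20/73.5 = 27.2% in the other, a gap of 6.5 points.
- Shift in the estimate = 0.0647 × g: 0.03 SD at g = 0.5 and 0.06 SD at g = 1.0.

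Scenarios A and B are alternatives. The article says only that separate randomisation made equal division more likely, which does not settle which one applies. Their figures must not be added together.

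**The case against.** The strongest objection is that the harm does not follow from the test as planned. A reader might infer from the stated reason for stratifying that hospital differences inflate the error of the planned test or bias its estimate. The article does not support that. It expects the hospitals to differ on characteristics that might affect the behavior. It does not say that they differ on the outcome itself, and still less on 8-week change. A constant difference cancels. This part of the objection stands, and it confines the point to a hospital difference in change.

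A second stronger reading is that the standard errors are wrong for the randomisation used and that imbalance is also likely. Each half needs a different allocation method, so both cannot hold together. The 0.03 to 0.06 SD shift is chance error that a valid test already allows for. It is not bias. Differential dropout by hospital could also unbalance the analysed set, but the article gives no dropout figures by hospital, so nothing can be built on that.

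It can also be said that two conditional sentences in a journal article leave covariates to the analysis plan. This does not remove the point, because the article names the two factors and so fixes a model without hospital.

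**Conclusion.** The mismatch is real: hospital shapes the randomisation for a stated prognostic reason and is absent from the stated model. The consequence is minor.

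- If the hospitals do not differ in pre-post change, nothing is lost.
- If they differ by 0.5 to 1.0 SD in change and arms are balanced within hospital, the test is conservative (about 4.5% to 3.3%), and about 0.4 to 2 points of power are lost from 95%.
- If allocation was by coin flip, the size is correct, and adjustment would remove a chance shift of about 0.03 to 0.06 SD under a 14/20 split.

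In neither case is type I error inflated, and no figure stated in the article changes. The sizes rest on the assumed range for g and on d back-calculated from the sample size, and they are for one outcome at a time. The value of adjusting is a modest gain in efficiency and an analysis that matches the design.

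**What to change.** Add hospital (academic or general) as a between-subject factor, with its hospital × time term, to the planned repeated-measures models for all main and additional outcomes. Keep time × group as the tested effect, and leave out a group × hospital term. For each outcome this is equivalent to a change-score model with group and hospital as terms. The repeated-measures approach need not be replaced.

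State also how the Excel randomisation was done in each hospital (fixed equal numbers or independent draws) and the resulting split, so that a reader can tell which scenario applies.

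The cost is one degree of freedom per outcome. No new data are needed, since hospital is known for every participant from the randomisation. The article's Results section says that outcomes were evaluated from April 2020 and results submitted in September 2020. If the analysis has already been run without hospital, the adjusted version should be reported as a disclosed additional analysis beside the planned one.

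### Training is given in group sessions in one arm only, but the stated time × group analysis treats all physicians as independent; if change is correlated within sessions, type I error exceeds 5%

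*Protocol article*

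**What the plan says.** Randomization is of individual physicians, done separately in each hospital (Step 5: Implementation). On delivery, Step 4 says: "The intervention consisted of a 4-hour group training session for diverse groups of physicians with a pre- and postmeasure". The session combines theory, reflection, exercises and goal setting. Step 5 adds: "In total, 7-14 physicians were planned to attend each training session". Four weeks on self-set goals and a coaching conversation by phone follow. According to the Abstract, the waitlist-control group received no training; both groups get the posttest link 8 weeks after the pretest.

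For the analysis, the article states: "we are planning to conduct 2-way, repeated-measures multivariate analyses of variance in SPSS", to assess the time × group interaction on the main and additional outcomes, followed by repeated-measures ANOVA within the groups. The assumptions to be checked are outliers, normality and sphericity. No session factor, random effect or cluster-robust variance is named.

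The Participants section gives 95% power and a two-sided 5% level, "Assigning equal numbers of participants to the intervention and control groups", and an effect "based on the effects of job crafting training interventions on job crafting behavior", which led to: "a total of 120 physicians (60 in each group) were needed". It mentions no ICC or design effect. The Discussion considers contamination between arms but not dependence within sessions.

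**The concern.** Physicians trained in the same session share the same half day and do the same exercises together. Their changes from pretest to posttest may therefore resemble one another more than those of physicians from different sessions. Individual randomization does not prevent this, because the correlation arises after allocation, through delivery. Controls have no such grouping before the posttest.

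A repeated-measures (M)ANOVA with time and group as its only factors handles the correlation between the two measurements of one physician, but takes different physicians as independent. None of the planned assumption checks would reveal session clustering. At stake are the standard error, the confidence interval and the error rate of the comparison on which the conclusions on job crafting, career self-management and employability will rest.

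**Working it through.** **Inputs from the article.** 60 per group, two-sided 5%, 95% power, 20% dropout, sessions of m = 7 to 14, clustering in the intervention arm only.

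**Input assumed.** The ICC ρ of the pre-post change within a session, taken as 0.01 to 0.10. The article gives no value. The ICC of change is the relevant one because the test is time × group.

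**Step 1: the stated sample size.** 120 / (1 − 0.20) = 150, so the recruitment target reproduces. The figure of 120 cannot be reproduced, because no effect size is stated. Solving backwards under independence: d = (1.960 + 1.645) × √(2/60) = 0.658 (0.664 with the t distribution). This shows what d would be without clustering; it does not show that the calculation left clustering out.

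**Step 2: standard error and type I error.** With equal total variance in both arms:

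- design effect in the intervention arm: DE = 1 + (m − 1)ρ
- ratio of true to nominal standard error: R = √((1 + DE)/2)
- type I error: 2 × (1 − Φ(1.96/R))

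For m = 10 and ρ = 0.05: DE = 1 + 9 × 0.05 = 1.45; R = √(2.45/2) = 1.107; 1.96/1.107 = 1.771; type I error 7.7%.

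| m | ρ | DE | R | Type I error |
|---|---|---|---|---|
| any | 0 | 1.00 | 1.000 | 5.0% |
| 7 | 0.01 | 1.06 | 1.015 | 5.4% |
| 7 | 0.05 | 1.30 | 1.072 | 6.8% |
| 7 | 0.10 | 1.60 | 1.140 | 8.6% |
| 10 | 0.01 | 1.09 | 1.022 | 5.5% |
| 10 | 0.05 | 1.45 | 1.107 | 7.7% |
| 10 | 0.10 | 1.90 | 1.204 | 10.4% |
| 14 | 0.01 | 1.13 | 1.032 | 5.8% |
| 14 | 0.05 | 1.65 | 1.151 | 8.9% |
| 14 | 0.10 | 2.30 | 1.285 | 12.7% |

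Simulating an unadjusted t-test (40,000 runs per setting) gave 5.2% to 12.9% for ρ of 0.01 to 0.10, and 4.9% to 5.1% at ρ = 0.

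**Step 3: power of a test that allows for sessions.** With k = 60/m sessions, the Satterthwaite degrees of freedom are (1 + DE)² / (DE²/(k − 1) + 1/59), and the noncentrality is 0.658 / √((1 + DE)/60).

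- m = 10, ρ = 0.05: k = 6; df = 6.00 / (0.4205 + 0.0169) = 13.7; noncentrality 0.658/0.202 = 3.26; power about 86%.
- m = 14, ρ = 0.10: k = 4.3; df about 6.7; noncentrality 0.658/0.2345 = 2.81; power about 67%.

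With a normal critical value these would be 90% and 80%; the difference is the price of having few sessions. All four figures rest on the d of Step 1.

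**Step 4: which random effect repairs the test.** Suppose the model for physician i in session j at time t contains a session intercept u_j that is the same at both times. The change is Y_ij1 − Y_ij0, and u_j − u_j = 0. Such an intercept therefore leaves the standard error of time × group uncorrected. The random effect must act on the change, that is, vary by session and time.

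**The case against.** The case against runs as follows. The ICC is unknown and may be low: there is one half-day session, the groups are described as diverse, goals are set individually, coaching is by phone, and the outcomes are self-reported some weeks later. At the low end the inflation is trivial, and the 12.7% figure pairs the largest session with the highest assumed ICC. Randomization is individual, so session grouping does not in itself bias the estimated effect; only its precision is in question. With so few sessions, the session variance will be poorly estimated. Data collection ended in March 2020 and results were submitted in September 2020, so the sample size can no longer change.

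All of this stands, and it makes the claim conditional. It does not supply a reason to fix the ICC at zero, which is what the stated model does.

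A reader might infer three stronger things that the article does not support.

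- That the type I error is certainly above 5%. It is so only if the ICC of change is positive.
- That the sample size was calculated with no design effect. The article only fails to mention one. Sixty per group fits d of about 0.66 under independence, but equally d = 3.605 × √(2.45/60) = 0.73 with a design effect of 1.45 in the intervention arm.
- That a shared trainer or a group discussion causes the correlation. The article does not say who led which session, and it mentions a group discussion only for the evaluation of the pilot. The documented ground is the shared session with its exercises.

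**Conclusion.** The point holds in conditional form and should be fixed. The Data Analysis section names a concrete model, so this is not a detail left to an analysis plan, and that model omits a level of grouping which the article's own account of delivery creates in one arm. If change is positively correlated within sessions, the true standard error of the time × group effect is about 1.015 to 1.285 times the nominal one, and type I error is about 5.4% to 12.7% rather than 5%, with 7.7% as the middle case. These figures rest on an assumed ICC of 0.01 to 0.10, sessions of 7 to 14, equal total variance in both arms and clustering in the intervention arm only. The direction is firm for any positive ICC; the size is not known.

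**What to change.** In Data Analysis, analyse each main outcome as the change score, or as the posttest adjusted for the pretest, with a random session effect in the intervention arm only, each control as a singleton, and Satterthwaite or Kenward-Roger degrees of freedom. A session-by-time random effect in the repeated-measures model is equivalent to the change-score form; a time-constant session intercept is not enough. Report the session ICC of each main outcome with its interval. In Participants, state that the 95% power assumes no within-session correlation, or, if an allowance was made, what it was.

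The model change is one term and can be fitted in SPSS MIXED. The cost is wider intervals and few degrees of freedom: 60 to 70 trained physicians give about 4 to 10 sessions (60/14 = 4.3 to 70/7 = 10), with the loss of power shown above if d is about 0.66. The ICC itself will be imprecise, which is why its interval should be shown. One point needs confirmation by the sponsor: the article describes codes that link pretest to posttest and says that the material was anonymized, but does not say that session membership was recorded with the survey data.
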